## Abstract

**Background:**

Hepatocellular carcinoma (HCC) accounts for 75–85% of primary liver cancers and is prevalent in the Asia-Pacific region. Till now, trans-arterial chemoembolization (TACE) is still one of common modalities in managing unresectable intermediate-stage HCC. However, post-TACE residual viable HCC is not uncommon, resulting in unsatisfied overall survival after TACE alone. Recently, stereotactic ablative radiotherapy (SABR) has been suggested to manage HCC curatively. However, evidence from phase-III trials is largely lacking.

Hence, the present phase III randomized trial is designed to compare clinical outcomes between SABR and re-TACE for unresectable HCC patients who had incomplete response after initial TACE.

**Methods:**

The present study is an open-label, parallel, randomized controlled trial. A total of 120 patients will be included into two study groups, i.e., SABR and re-TACE, with a 1:1 allocation rate. A 3-year allocating period is planned. Patients with incomplete response after initial TACE will be enrolled and randomized. The primary endpoint is 1-year freedom-form-local-progression rate. Secondary endpoints are disease-progression-free survival, overall survival, local control, response rate, toxicity, and duration of response of the treated tumor.

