#### Primary objective

The main goal of the present study is to assess the role of SABR in HCC patients who have incomplete response after initial TACE. Patients treated with re-TACE will be allocated into the active comparator group. Freedom form local progression (FFLP) is the primary end point.

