## Outcome measures

### Primary outcome measure

The primary outcome measure is freedom from local progression (FFLP) [24]. FFLP will be defined as time with no in-field progressive disease. Response for target lesions will be defined according to the RECIST version 1.1 and modified RECIST (mRECIST) [52]. The target lesions should show intra-tumor arterial enhancement on contrast-enhanced CT or MRI and can be accurately measured in at least one dimension as 1 cm or more [53, 54].

Several tumor responses will be defined by two independent physicians (one hepatic-specific radiologist and one radiation oncologist): complete response (CR), total disappearance; partial response (PR), 30% decrease in single longest diameter (SLD) of contrast-enhanced part; stable disease (SD), neither partial response nor progressive disease met; and, progressive disease (PD), 20% increase of SLD or new lesion(s).

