### Sample size calculation

According to prior studies, response rates have been reported: 38% in patients treated with TACE alone [37] and 76.6% in those treated with TACE then salvage SABR [44]. As a result, an absolute increase of 30% in response rate will be considered as having a clinical significance. By using probability of type I error (α, 0.05; and, power [1 - β], 80%), 46 patients will be required in both the two study groups, resulting in a total study cases of 92. With an estimate of drop-out rate of 20%, we will enroll an additional 24 patients to counter potential attrition, reaching a final sample size of 120.

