## Statistical methods and data analysis

Data will be analyzed by using SAS (version 9.2; SAS Institute, Inc., Cary, NC, USA) and SPSS (version 17, SPSS Inc., Chicago, IL, USA), accordingly. Demographic data will be examined differences between groups by using chi-square test (for categorical variables) and Wilcoxon rank sum test (for continuous variables).

Time-to-event outcomes, such as FFLP (time to in-field target-tumor progression), progression-free (time to local, regional, or distance progression) and overall survival (time to patient death from any cause) will be evaluated by using Kaplan-Meier method. Curve difference between groups will be assessed by using log-rank test. Multivariate analysis will be done by using Cox proportional hazard regression. Hazard ratio with 95% confidence interval will be provided in conjunction with *p* values to demarcate effective size. All statistical analysis will be performed by using a two-tailed approach. A *p* value of < 0.05 will be considered as having a statistical significance.

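### The abstract makes the 1-year FFLP rate the primary endpoint, but the only planned test compares whole FFLP curves, and nothing says which result decides the trial

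*Protocol article*

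**What the plan says.** Four places in the protocol article bear on the primary result.

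- Abstract, Methods: "The primary endpoint is 1-year freedom-form-local-progression rate". This is a proportion at a fixed time.
- Primary objective: "Freedom form local progression (FFLP) is the primary end point". No time point is given.
- Primary outcome measure: "FFLP will be defined as time with no in-field progressive disease". This is a time variable, again without a landmark.
- Statistical methods and data analysis: FFLP is listed under "Time-to-event outcomes, such as FFLP (time to in-field target-tumor progression" and is to be described by Kaplan-Meier. Then: "Curve difference between groups will be assessed by using log-rank test". The effect measure comes from Cox regression: "Hazard ratio with 95% confidence interval will be provided in conjunction with" p values. Tests are two-sided at 0.05.

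The section on timing of assessments has data collected every 3 months up to 2 years, and the section on secondary outcomes continues imaging every 6 months for 3 more years. The statistics section does not say at what follow-up time the FFLP curves are cut for the comparison. The 1- and 2-year time points in the secondary outcome section belong to the secondary outcomes only.

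**The concern.** A 1-year rate and a whole-curve comparison are different quantities. The first uses only what has happened by month 12. The log-rank test weighs every event up to the end of follow-up, and its natural effect measure is the hazard ratio. A significant log-rank result does not establish a difference in the 1-year rate, and a clear 1-year difference can go with a non-significant log-rank test.

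The article therefore names one quantity as its primary endpoint and plans a test of another. If the results pointed different ways, a reader could not tell from the article whether the trial had met its primary endpoint. Treatment is open-label, so it is worth removing any room to settle this after the data are known.

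**Working it through.** **1. The plan's own figure.** The sample size section gives 46 per group. With response rates of 38% and 38% + 30% = 68%, two-sided α 0.05 and power 80%, the unpooled formula is

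n = (1.96 + 0.842)² × (0.38×0.62 + 0.68×0.32) / 0.30² = 39.5.

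The continuity correction, n/4 × [1 + √(1 + 4/(n×0.30))]², gives 45.95, so 46. The figure reproduces. It rests on response rate, which is neither version of FFLP, so the calculation cannot show which version was meant. That mismatch is a separate matter.

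**2. The two readings as statistics.**
- 1-year rate: Z = (S₁ − S₀)/√(V₁ + V₀), with S the Kaplan-Meier estimate at 1 year in each arm and V its Greenwood variance.
- Log-rank: Z = Σ(observed − expected)/√V, summed over all event times up to the data cut.

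**3. How different their demands are.** The article gives no FFLP rates by arm. Assume 60% v 80% at 1 year with proportional hazards, so HR = ln 0.80/ln 0.60 = 0.44.
- 1-year rate, 80% power, two-sided 0.05: 82 per arm (two proportions, pooled variance).
- Log-rank: 4 × (1.96 + 0.842)²/(ln HR)² = 46 events. Over 2 years the expected event fraction is 1 − (0.60² + 0.80²)/2 = 0.50, so 46/0.50/2 = 46 per arm.

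**4. How often the verdicts differ.** Simulation: 4,000 trials per scenario, 60 per arm, administrative censoring at 2 years, exponential loss of 20% by 2 years, each test two-sided at 0.05. All rates and curve shapes are assumptions.

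| Assumed FFLP | Log-rank significant | 1-year test significant | Verdicts differ |
|---|---|---|---|
| 60% v 80% at 1 year, proportional hazards | 85% | 67% | 23% |
| 60% v 80% at 1 year, both 45% at 2 years | 11% | 67% | at least 67 − 11 = 56% |
| 75% in both at 1 year, 40% v 65% at 2 years | 55% | 5% | at least 55 − 5 = 50% |

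The last two entries are lower bounds, because verdicts must differ at least as often as the two powers differ. Direct counts over non-proportional scenarios of this kind were 55–73%. With 48 per arm (120 × 0.8/2) and no other loss, the verdicts differed in 16–26% of trials for proportional-hazards effects of 20–25 points, and in 57–72% for curves that converge or separate after 1 year.

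**5. Dependence on the horizon.** If the log-rank test is cut at 1 year instead of 2, disagreement falls to about 4–5% in the proportional-hazards case and to 1–4% in the other scenarios. The article states neither cut.

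**6. Type I error if either result may be claimed.** With 60% in both arms, each test alone is significant in 5–6% of trials. At least one is significant in 7.4–8.6% across runs, or about 8%.

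The simulations ignore the 3-monthly imaging grid and deaths without local progression.

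**The case against.** The strongest reply is that the statistics section states only one between-group test. The ordinary reading is then that log-rank decides and the 1-year rate is a number read off the Kaplan-Meier curve. The objectives, outcome and statistics sections agree with one another, and the conflict comes from a single line of the abstract of a condensed article. This is plausible, and the preferred fix adopts it. It does not remove the point: that line calls the 1-year rate the primary endpoint, and no section reduces it to a summary. This is a conflict between stated texts, not a detail left to an analysis plan.

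A reader might infer three stronger things that the document does not support.

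- *That the plan contains two rival primary tests.* It does not. No test of the 1-year rate is written anywhere.
- *That non-proportional curves would give opposite conclusions.* They can split the verdicts into significant and non-significant, but need not. Both tests being significant in opposite directions occurred in at most 0.03% of the non-proportional runs. Nothing in the article suggests that such curve shapes are expected.
- *That the log-rank test is planned over 2 years.* Two years is the data-collection schedule, and imaging continues beyond it. The large disagreement figures depend on that assumed horizon.

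It also stands that the inflation from choosing afterwards is modest.

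**Conclusion.** The point holds as an inconsistency about the primary result. The abstract names the 1-year FFLP rate, the body defines and tests FFLP as a time-to-event outcome, no analysis horizon is stated, and nothing says which result decides the trial.

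Under the assumed 60% v 80% with proportional hazards and 2 years of follow-up, the choice changes the verdict in roughly one trial in four or five. It can do so in more than half where the curves converge or separate after 1 year, and it hardly matters if the log-rank test is cut at 1 year. The cost in type I error of choosing after the fact is about 3 percentage points (5% to about 8%). These sizes belong to the assumed rates and shapes, but the inconsistency itself needs no assumption.

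Severity: should-fix. A natural reading reconciles most of the text, and one clarification would settle it.

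**What to change.** State one primary analysis, in the same terms, in the abstract, the primary objective, the primary outcome measure and the statistics section.

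- *Preferred:* the primary endpoint is FFLP from randomisation over a stated follow-up period, compared by the planned two-sided log-rank test, stratified by BCLC stage and total bilirubin. Report the 1-year Kaplan-Meier FFLP in each arm, with a 95% CI for the difference, as the summary. Stratifying is a recommendation that matches the test to the randomisation; it is not needed to resolve the inconsistency.
- *If the 1-year rate is to stay primary:* make the difference in 1-year Kaplan-Meier FFLP the primary test, with its 95% CI, and the log-rank test secondary.

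Either choice should be dated and made before any comparison of outcomes by arm. It costs wording in the protocol and analysis plan, with IRB re-approval, which the article requires for changes to outcome analyses. It needs no extra data or visits.

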**Discussion:**

SABR has been reported as an effective modality in managing intermediate-stage HCC patients, but evidence from phase-III randomized trials is largely lacking. As a result, conducting randomized trials to demarcate the role of SABR in these patients is warranted, especially in the Asia-Pacific region, where HBV- and HCV-related HCCs are prevalent.

**Trial registration:**

Before enrolling participants, the present study was registered prospectively on ClinicalTrials.gov (trial identifier, NCT02921139) on Sep. 29, 2016. This study is ongoing.

## Background

### Background and rationale

#### Hepatocellular carcinoma (HCC)

Liver cancers are sixth cause of cancer incidence and third cause of cancer death over the world – estimated 818,000 patient died in 2013 [1]. Of these, HCC accounts for 75–85% of primary liver cancers and is the third cause of cancer death in the Asia-Pacific region, where are also the endemic areas of chronic viral hepatitis (mainly hepatitis B and C) [2–4], leading to a combination of liver function impairment, such as liver cirrhosis, in HCC patients.

In addition to adverse effects of chronic viral hepatitis, most HCC patients were classified as intermediate to advanced stage at the time of diagnosis. As a result, though many treatment modalities can be chose for these patients [5, 6], 5-year survival rate is still poor, being less than 20% [7]. Note that the main failure pattern after tumor resection is intra-liver recurrence [8]. This observation still holds true for patients who undergo TACE or other local treatment modality alone.

#### Trans-arterial chemoembolization (TACE)

Although a Cochrane review failed to show significant survival benefits of TACE for unresectable HCC patients [9], TACE is still the most widely used locoregionally life-extending treatment for HCC patients with intermediate stage [6]. This recommendation is mainly based on six randomized prospective studies that demonstrate a survival benefit of TACE when compared with best supportive care or suboptimal therapies [10]. Note that most previously mentioned studies are investigated about ‘unresectable’ rather than “intermediate stage” HCC that classified by BCLC classification [11].

#### Stereotactic ablative radiotherapy (SABR)

When compared with conventional RT, SABR used a very precise way to delivering high dose of irradiation in a limited number of treatment fractions, demonstrating a large therapeutic benefit [12]. For maintaining a high precision of SABR, reliable immobilization, daily on-board image guidance, respiratory gating, and 360-degree Volumetric-Modulated Arc Therapy (VMAT) techniques are conducted clinically [13].

Recently, SABR, or alternatively named stereotactic body radiotherapy (SBRT), has been reported as a curative modality in managing early-stage HCC [14–21]. Moreover, the role of SABR is gradually defined in HCC patients with relatively large size (i.e., > 3 cm) [22], advanced [23], unresectable [24], and oligometastatic disease [25]. Remarkably, a role of SABR has been also reported in post-TACE HCC patients, in terms of adjuvant [26] or salvage setting [27, 28]. However, till now, level-III evidence is still largely lacking, rising an importance to conduct randomized trials for this issue [29–31].

Most studies showed that local control of inoperable HCC treated with SABR are about 72–89.8% at 1 year and 64% at 2 years, respectively [32, 33]. For selected patients, local control can be achieved as high as 99% at 1 and 2 years, respectively [34]. These outcomes of SABR were comparable with RFA, particularly for tumors > 2 cm [24, 35]. More notably, SABR showed a benefit of limited toxicities, even in elderly HCC patients [36].

### Rationale to conduct SABR for incomplete TACE

As mentioned above, TACE is effective for managing HCC patients with early to intermediate stage. However, TACE alone cannot achieve satisfactory complete tumor response rate, demonstrating median response and complete response rates after TACE was 38% (range 3–86%) and 0 (range 0–35%), respectively [37]. The unsatisfactory complete response suggested the concept of combining local therapy to improve local control.

In this regard, TACE combined with RFA has been reported to be useful in local tumor control [38, 39]. Recently, image-guided high-precise radiotherapy, i.e., SABR, has been reported to play a role in managing incomplete TACE [27]. However, evidence from randomized phase III studies is largely lacking.

Hence, the main reason to conduct SABR for unresectable HCC patients who had incomplete response after TACE is to increase treatment response and to prolong patient survival [24, 26, 28, 40–45]. In addition, post-TACE embolized materials were also useful to guide dose delivery of SABR, enhancing targeting precision.

### Objective and hypothesis

Taken together, conducting a randomized clinical trial to test the role of SABR in eradicating HCC – particularly for post-TACE residual tumors – is strongly encouraged [29–31]. As a result, the present phase-III trial intends to compare clinical outcomes between TACE plus SABR and TACE plus re-TACE for HCC patients who had post-TACE residual tumors.

#### Primary objective

The main goal of the present study is to assess the role of SABR in HCC patients who have incomplete response after initial TACE. Patients treated with re-TACE will be allocated into the active comparator group. Freedom form local progression (FFLP) is the primary end point.

#### Secondary objectives

Several secondary objectives are as follows: overall survival, tumor response rate, duration of tumor response, and side effects.

#### Hypothesis

We hypothesize that SABR is able to demonstrate better clinical outcomes than that of re-TACE for HCC patients who have incomplete response after their initial TACE, in terms of tumor response, local-progression-free and patient survival. In addition, limited treatment toxicities are expected to be observed in patients treated with SABR, as reported previously [45].

#### Trial design

The present study is a prospective, parallel, and open-label randomized controlled trial (RCT). An allocation ratio of 1:1 will be applied between the two study groups, i.e., SABR and re-TACE.

## Methods/design

### Ethic and consent

The present study will be conducted after a formal approval of Institute Review Board (Dalin Tzu Chi Hospital, Buddhist Tzu Chi Medication Foundation; approval number: A10502001). Important protocol modifications, e.g., changes to eligibility criteria or outcome analyses, will be re-submitted to IRB and implemented only after a re-approval of IRB.

Written informed consent will be obtained for each participant. Details of the trial process, including pros and cons of interventions, will be explained by both physician and study nurse. Whole-day contact information of investigators will be provided for all participants and their families. Obtained data will be kept in a security locker. The present protocol is reported according to recommendation of SPIRIT 2013 [46]. Final analyses and results will be submitted for publication on a peer-reviewed journal after completion of the study.

### Study setting

The present study will be conducted at a single regionally academic institute (i.e., Dalin Tzu Chi Hospital, Chia-Yi, Taiwan). Inter-institute cooperation for enrolling potential patients may be done under formal supervision of IRBs.

### Inclusion criteria

Several inclusion criteria will be as follows.Patients who are diagnosed with HCC via one of the following methods:radiographically typical enhancement pattern with arterial enhancement and portal or delayed washed out on triple-phase dynamic Computed Tomography (CT) or Magnetic Resonance Imaging (MRI), with or without an elevated value of alpha-fetoprotein (AFP); or,histopathological confirmation of HCC.HCC patients who are treated with initial TACE with incomplete response (i.e., partial response, stable disease, or disease progression).Age ≥ 20 years old.BCLC stage A-B and Child-Pugh score A-B.Unresectable tumors, medically inoperable status, or refusal of surgery.Clinically feasible for SABR or re-TACE.SABR can be applied within 6 weeks of registration.ECOG 0–1.Life expectancy > 3 months. Negative pregnancy. No prior treatment, except for surgical resection and radiofrequency ablation (RFA). Criteria of allowed laboratory data were as follows:hemoglobin, ≥8.0 g/dl (may be post-transfusion if clinically indicated);total bilirubin, ≤3.0 mg/dl;AST (SGOT), ≤5-fold institutional upper limit of normal range;ALT (SGPT), ≤5-fold institutional upper limit of normal range;absolute neutrophil count, ≥1000/cumm;platelet count, ≥20,000/cumm (may be post-transfusion if clinically indicated); and,prothrombin time, international normalized ratio, ≥1.7.

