### Arm B, the active comparator group: re-TACE (planned *n* = 60)

TACE will be conducted by using a catheter to deliver chemotherapeutic agent and embolic materials into the blood vessels that supply to the tumor. Generally the procedure time will be completed within 1–2 h, and the hospitalization course will be 3 days.

Before each TACE, laboratory data will be checked, and abdominal images will be reviewed. Treatment plan will be discussed and determined by radiologists and gastrointestinal physicians. The planned catheter-inserted site will be the groin. A guide wire will be inserted into the femoral artery. A curve Angiographic Catheters (COOK MEDICAL INC., Bloomington, USA) followed by a superselective microcatheter (Terumo®, Tokyo, Japan) will be sent to the target artery in the liver.

As the catheter approach to the target, several series of angiography will be done to identify the lesion sites. After the target site is determined, catheter will be inserted to the feeding artery branch. Chemotherapy agent (Epirubicin, 30 mg), oil-based radio-opaque contrast agent (LIPIODOL® [ethiodized oil], 5–10 ml, according to tumor size), several 1 × 1 mm Sterile Sponge (Gelfoam®), contrast (XENETIX 350 [350 mg/ml], and solution for injection 10 ml) will be mixed together and then injected to the tumor site.

Post-procedure care will be prescribed, including keeping absolute bed rest for 12 h after the procedure. The incision wound will be compressed by a 2-Kg sandbag for 4–6 h for hemostasis. The medical care team will closely monitor vital signs, pulse of the distant limb, and awareness of whether TACE-associated complication occurred, such as nausea, vomiting, and allergic reactions. Proper treatments will be provided if complication occurs.

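### The INR inclusion limit is printed the wrong way round (≥1.7), very probably a misprint; read literally it bars normal clotting and sets no ceiling

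*Protocol article*

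**What the plan says.** The protocol article, Inclusion criteria, introduces a list of seven laboratory limits with "Criteria of allowed laboratory data were as follows". The items are therefore conditions for entry, not grounds for exclusion. Among them are "total bilirubin, ≤3.0 mg/dl", "AST (SGOT), ≤5-fold institutional upper limit of normal range" and "platelet count, ≥20,000/cumm". The last item is "prothrombin time, international normalized ratio, ≥1.7".

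The same section also requires BCLC stage A or B, Child-Pugh class A or B, and a patient who is "Clinically feasible for SABR or re-TACE". For the re-TACE arm, the section on Arm B states "Before each TACE, laboratory data will be checked" and describes the access route: "A guide wire will be inserted into the femoral artery".

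**The concern.** A raised INR means slower clotting, so an eligibility limit on INR should be a ceiling. The printed sign makes it a floor. A reader who applies the line as written would turn away patients with normal clotting and admit those with prolonged clotting, however prolonged.

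What is at stake is bleeding safety and a clear definition of the trial population. The comparator arm involves femoral artery puncture, and the platelet limit, which points the right way, already admits counts down to 20,000/cumm. The INR line is the only numerical limit on prothrombin time or INR in the article, and as printed it protects nobody. Enrolment has been open since December 2016 (Current status), and the article foresees cooperation with other institutes for recruitment (Study setting). Screening staff and outside referrers should not have to guess the sign of an entry criterion.

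**Working it through.** There is no figure to reproduce. The check compares the direction of each limit with the direction in which the measure becomes harmful, and then looks for any other text that would correct or replace the INR line.

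**Step 1: the seven limits in the Inclusion criteria.**

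| Measure | Harmful direction | Printed limit | Side excluded |
|---|---|---|---|
| Haemoglobin | low | ≥8.0 g/dl | abnormal |
| Absolute neutrophil count | low | ≥1000/cumm | abnormal |
| Platelets | low | ≥20,000/cumm | abnormal |
| Total bilirubin | high | ≤3.0 mg/dl | abnormal |
| AST | high | ≤5 × upper limit of normal | abnormal |
| ALT | high | ≤5 × upper limit of normal | abnormal |
| INR | high | ≥1.7 | **normal** |

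Three low-is-worse limits carry ≥, three high-is-worse limits carry ≤, and one high-is-worse limit carries ≥: 3 + 3 + 1 = 7. Six of the seven exclude the abnormal side and one excludes the normal side. Among the four high-is-worse measures, INR is the single exception.

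**Step 2: could the sign be a fault of text extraction?** This is unlikely. Both ≤ and ≥ come through sensibly in the other six items of the same list.

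**Step 3: does anything else state an INR limit?**

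- Exclusion criteria: no clotting limit.
- Table 1, notes b and c: PT/APTT and INR are listed as measurements, with no threshold.
- The requirement that treatment be clinically feasible, and the laboratory check before each TACE: neither gives an INR value.
- Child-Pugh A or B: restricts liver dysfunction only indirectly and is not an INR ceiling.

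**Step 4: the two readings.**

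- As printed (INR ≥1.7): every candidate below 1.7 is ineligible, and any value from 1.7 upward is allowed. That a normal INR is about 1.0 is general clinical knowledge and is not stated in the article. On that basis the printed rule shuts out all patients with normal clotting.
- Reversed (INR ≤1.7): the line becomes a ceiling and matches the bilirubin, AST and ALT limits. This is almost certainly what was meant.

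**Step 5: can past screening be checked if that proves necessary?** Yes. INR belongs to the serum biochemistry panel (Table 1, note c), which is ticked in all 12 columns: screening plus V0 to V10, or 1 + 11 = 12.

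**The case against.** The strongest reply is that this is a one-character proofreading slip in a journal article. The intended direction is plain from the neighbouring lines, the approved protocol may print it correctly, and nothing shows that the printed sign was ever used. The literal rule would also be hard to follow by accident. Clinical staff would notice that it admits only patients with prolonged clotting. Every candidate has already had an initial TACE, Child-Pugh C is excluded, and radiologists and gastrointestinal physicians decide on each TACE after reviewing laboratory results and images. The platelet limit is a separate matter, and counting signs does not measure harm to patients.

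Most of this stands, and it limits how serious the point is. It makes literal use unlikely, and it means that no harm can be claimed from the document alone. The low platelet limit shows why clotting matters in this population, but it is no evidence about the INR sign. The reply does not remove the error. The article does not leave the threshold to a fuller document: it states a number with a sign, and the sign is wrong. None of the safeguards supplies the missing ceiling.

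**Conclusion.** The concern holds. The INR criterion is wrong as printed, very probably through a misprint, and should be corrected. It affects 1 of 7 laboratory limits. Followed exactly, it excludes everyone with an INR below 1.7 and leaves the article without any INR ceiling.

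The conclusion rests on the list's own pattern and on the fact that a high INR is the harmful direction. That ≤1.7 was intended is a strong inference, not something the article proves; for instance, it cannot show whether < or ≤ was meant. Whether any patient was screened against the wrong sign depends on the approved text and the working checklist, neither of which is shown. The primary endpoint, the sample size calculation and the planned analyses do not depend on this line.

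**What to change.** 1. Compare the INR line with the IRB-approved protocol and with the eligibility checklist in use.
2. If the approved text gives 1.7 as an upper limit, publish an erratum changing ≥1.7 to ≤1.7 (or to the exact approved wording), and make sure the checklist agrees.
3. If the approved text carries the printed sign, submit an amendment. The section on ethics and consent requires changes to eligibility criteria to be re-approved before use. Also review the screening INR of patients already enrolled.

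The cost is low: one character and a checklist check in the likely case, or a short amendment in the other. The review in step 3 needs no new data, because INR is scheduled at screening and at baseline.

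As a separate tidy-up, the same erratum can correct the bilirubin unit. The sections on randomization and on criteria for discontinuing or modifying interventions print g/dl, where the Inclusion criteria correctly use mg/dl.
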